## SSQ: PRIVATE DRUG SHOPS (2)

|                       |                    |                          |
|-----------------------|--------------------|--------------------------|
| Drug shop code | Provider ID | Date              |
| [ ][ ]                | [ ][ ][ ][ ]       | [ ][ ] / [ ][ ] / [ ][ ] |
|                       |                    | day month year           |

## SECTION 2: SUPPLY MANAGEMENT

|                                                                                               |                                                                |        |
|-----------------------------------------------------------------------------------------------|----------------------------------------------------------------|--------|
| 1. 'Does this drug shop typically stock artemether-lumefantrine?'                      | 1 = Yes    88 = Don't know
2 = No    99 = Refused to answer | [ ][ ] |
| If yes, go to Qn 2, otherwise skip to Qn 5                                             |                                                                |        |
| 2. 'Is artemether-lumefantrine available today?'                                       | 1 = Yes    88 = Don't know
2 = No    99 = Refused to answer | [ ][ ] |
| 3. 'Have there been stock-outs of artemether-lumefantrine in the last 6 months?'       | 1 = Yes    88 = Don't know
2 = No    99 = Refused to answer | [ ][ ] |
| 4. 'Does this drug shop stock 'Green Leaf' artemether-lumefantrine supported by AMFm?' | 1 = Yes    88 = Don't know
2 = No    99 = Refused to answer | [ ][ ] |

## ARTEMETHER-LUMEFANTRINE BRANDS AVAILABLE

|                                     | Stock
1=Always
2=Sometimes
3=Never | Available today
1=Yes
2=No | Cost per unit
Ugandan shillings | Unit
1=Package
2=Tablet |
|-------------------------------------|----------------------------------------------------|-----------------------------------------|-------------------------------------------|--------------------------------------|
| 5a. Coartem (Novartis, Switzerland) | [ ][ ]                                             | [ ][ ]                                  | [ ][ ][ ], [ ][ ][ ][ ][ ]                | [ ][ ]                               |
| 5b. Lumartem (Cipla, India)         | [ ][ ]                                             | [ ][ ]                                  | [ ][ ][ ], [ ][ ][ ][ ][ ]                | [ ][ ]                               |
| 5c. Lomart (Agog, India)            | [ ][ ]                                             | [ ][ ]                                  | [ ][ ][ ], [ ][ ][ ][ ][ ]                | [ ][ ]                               |
| 5d. Artefan (Ajanta Pharma, India)  | [ ][ ]                                             | [ ][ ]                                  | [ ][ ][ ], [ ][ ][ ][ ][ ]                | [ ][ ]                               |
| 5e. Lumiter (Macleods, India)       | [ ][ ]                                             | [ ][ ]                                  | [ ][ ][ ], [ ][ ][ ][ ][ ]                | [ ][ ]                               |
| 5f. Lonart (Milan Labs, India)      | [ ][ ]                                             | [ ][ ]                                  | [ ][ ][ ], [ ][ ][ ][ ][ ]                | [ ][ ]                               |
| 5g. Green leaf (AMFm)               | [ ][ ]                                             | [ ][ ]                                  | [ ][ ][ ], [ ][ ][ ][ ][ ]                | [ ][ ]                               |
| 5h. Other                           | [ ][ ]                                             | [ ][ ]                                  | [ ][ ][ ], [ ][ ][ ][ ][ ]                | [ ][ ]                               |
| 5i. Other                           | [ ][ ]                                             | [ ][ ]                                  | [ ][ ][ ], [ ][ ][ ][ ][ ]                | [ ][ ]                               |
| 5j. Other                           | [ ][ ]                                             | [ ][ ]                                  | [ ][ ][ ], [ ][ ][ ][ ][ ]                | [ ][ ]                               |

## OTHER ARTEMISININ-BASED COMBINATION THERAPIES

| 6. 'Does this drug shop typically stock other artemisinin-based drugs (ACTs)?'                                                                                                                         | 1 = Yes    88 = Don't know
2 = No    99 = Refused to answer | [ ][ ]                                             |                                         |
|---------------------------------------------------------------------------------------------------------------------------------------------------------------------------------------------------------------|----------------------------------------------------------------|----------------------------------------------------|-----------------------------------------|
| If YES, list other ACTs typically stocked at this drug shop, including:
artesunate + amodiaquine, dihydroartemisinin + piperaquine,
artemisinin + naphthoquine (ARCO), artesunate + mefloquine |                                                                |                                                    |                                         |
| Brand Name                                                                                                                                                                                             | Manufacturer                                            | Stock
1=Always
2=Sometimes
3=Never | Available today
1=Yes
2=No |
| 7a.                                                                                                                                                                                                           |                                                                | [ ][ ]                                             | [ ][ ]                                  |
| 7b.                                                                                                                                                                                                           |                                                                | [ ][ ]                                             | [ ][ ]                                  |
| 7c.                                                                                                                                                                                                           |                                                                | [ ][ ]                                             | [ ][ ]                                  |
| 7d.                                                                                                                                                                                                           |                                                                | [ ][ ]                                             | [ ][ ]                                  |
| 7e.                                                                                                                                                                                                           |                                                                | [ ][ ]                                             | [ ][ ]                                  |
| 7f.                                                                                                                                                                                                           |                                                                | [ ][ ]                                             | [ ][ ]                                  |
| 7g.                                                                                                                                                                                                           |                                                                | [ ][ ]                                             | [ ][ ]                                  |

**SSQ: PRIVATE DRUG SHOPS (3)**

|                                  |                                       |                                                              |
|----------------------------------|---------------------------------------|--------------------------------------------------------------|
| Drug shop code
[ ] [ ] | Provider ID
[ ] [ ] [ ] [ ] | Date
[ ] [ ] / [ ] [ ] / [ ] [ ]
day month year |
|----------------------------------|---------------------------------------|--------------------------------------------------------------|

**SECTION 2 cont: SUPPLY MANAGEMENT****OTHER ANTIMALARIAL DRUGS**

**7. 'Does this drug shop typically stock other malaria drugs?'** 1 = Yes 88 = Don't know  
2 = No 99 = Refused to answer [ ] [ ]

*If YES, review the list below and complete the information on stocking*

|                               | Stock                       | Available today |
|-------------------------------|------------------------------------|------------------------|
|                               | 1=Always
2=Sometimes
3=Never | 1=Yes
2=No          |
| 8a. Chloroquine               | [ ]                                | [ ]                    |
| 8b. Amodiaquine               | [ ]                                | [ ]                    |
| 8c. Sulfadoxine-pyrimethamine | [ ]                                | [ ]                    |
| 8d. Quinine oral              | [ ]                                | [ ]                    |
| 8e. Quinine injectable        | [ ]                                | [ ]                    |
| 8f. Artesunate injectable     | [ ]                                | [ ]                    |
| 8g. Primaquine                | [ ]                                | [ ]                    |
| 8h. Mefloquine                | [ ]                                | [ ]                    |
| 8i. Other                     | [ ]                                | [ ]                    |

**9. Please provide any additional comments about supply of drugs at this drug shop.**

**SECTION 3: PATIENT LOAD**

**1. "On average, how many people visit this drug shop each week?"** Total number of customers per week [ ] [ ]

**2. "Do you think that there has been a change in the number of people who visit your drug shop each week in the last year?"** 1 = Yes 88 = Don't know  
2 = No 99 = Refused to answer [ ] [ ]  
*If YES, go to Qn 3. Otherwise skip to next section.*

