**3. "If so, what kind of changes have you noticed?"**

1 = More customers come to the drug shop  
2 = Fewer customers come to the drug shop [ ] [ ]  
3 = More patients with malaria come to the drug shop  
4 = Fewer patients with malaria come to the drug shop [ ] [ ]  
5 = Customers ask for different drugs (*specify*) [ ] [ ]  
\_\_\_\_\_  
77 = Other \_\_\_\_\_  
88 = Don't know  
99 = Refused to answer

*Record all answers given*

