**SECTION 3 cont: PATIENT LOAD**

4. "What do you think is the reason for this change?"

5. Please provide any additional comments about patient load at this drug shop.

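### The drug-shop questionnaire asks about malaria customers and drugs requested only if total custom changed, so a shift within steady trade goes unrecorded in that section

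*Supplement*

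**What the plan says.** The private drug shop questionnaire, Section 3 (Patient load), runs as follows.

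- Qn 1 asks for the current average number of weekly customers.
- Qn 2 is a yes/no item, with codes for don't know and refused, on "a change in the number of people who visit your drug shop each week", with a one-year recall window. Its routing instruction is "If YES, go to Qn 3. Otherwise skip to next section".
- Qn 3 asks what kind of change was noticed. Besides more or fewer customers overall, its codes include "3 = More patients with malaria come to the drug shop", "4 = Fewer patients with malaria come to the drug shop" and "5 = Customers ask for different drugs".
- Qn 4 asks "What do you think is the reason for this change", and Qn 5 is an open item: "Please provide any additional comments about patient load at this drug shop".

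Secondary objective 4 (protocol section 3.2) includes impacts of the health facility intervention (HFI) on the private sector. Section 1.2 says the intervention is meant to draw people to health facilities and to improve the care of malaria and other febrile illness. Section 5.3.4 allows up to 10 drug-shop interviews. Section 5.7 places them about 9-12 months after roll-out and describes the questionnaire as a draft to be piloted and refined if needed.

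**The concern.** The filter and the items behind it measure different things. Qn 2 is about a headcount. Three of the Qn 3 codes are about who comes and what they ask for, and the code for different drugs is not a change in numbers at all. The authors evidently wanted to record such changes, but the routing reaches them only when total custom has also changed.

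This matters because a change in malaria customers is one of the changes the intervention could be expected to produce in the private sector. In Table 4.1 drug shops appear under this questionnaire only, with no in-depth interview and no focus group. Section 5.7 describes a single round with no baseline, so the shop worker's own report of change is the main evidence from the shops themselves. In a filtered-out shop, Qn 3 is blank whether malaria custom changed or not, and the two cases cannot be told apart at analysis.

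**Working it through.** No figure in the plan is at stake, so the check is a trace of the routing, followed by a search for the same information elsewhere in the form.

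**Step 1. Routing by answer to Qn 2**

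| Qn 2 answer | Qn 3 (kind of change) | Qn 4 (reason) | Qn 5 (comments) |
|---|---|---|---|
| 1 Yes | asked | asked | asked |
| 2 No | skipped | skipped | skipped |
| 88 Don't know | skipped | skipped | skipped |
| 99 Refused | skipped | skipped | skipped |

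**Step 2. Four kinds of shop, each answering correctly**

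| Total custom | Malaria custom or drugs requested | Qn 2 | Shift recorded in Section 3? |
|---|---|---|---|
| changed | changed | Yes | yes |
| changed | unchanged | Yes | none to record |
| steady | unchanged | No | none to record |
| steady | changed | No | **no** |

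The last row is the fault. It applies equally to a rise and to a fall in malaria custom.

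**Step 3. Can another item in the visible form recover it?** Qn 1 cannot: it is one current total with no malaria share and no earlier value. Section 2 covers stock. Section 4 asks which treatments are recommended now. The comment boxes at the end of Sections 2 and 4, and the Section 5 box, survive the skip but carry no prompt about change in customers. The pages shown begin at page (2), so page 1 cannot be checked.

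**Step 4. Size.** If other trade is constant, the proportional change in total custom is s × f, where s is the malaria share of customers and f is the proportional change in malaria customers. The documents give neither. As an assumption only, with s from 20% to 40% and f from 25% to 50%:

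- 0.20 × 0.25 = 5%
- 0.40 × 0.25 = 10%
- 0.20 × 0.50 = 10%
- 0.40 × 0.50 = 20%

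So under those assumptions total custom moves by 5% to 20%. This shows that the total moves less than the malaria part. It does not show whether a shop worker would report such a change, nor how many shops would be filtered out. If other trade offsets the change, the total need not move at all, and a change only in the drugs requested moves it by nothing.

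One shop filtered out of the maximum of 10 is 1/10 = 10% of the planned sample.

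**Step 5. A comparison within the protocol.** The focus group guide for community health workers asks, with no filter on numbers, whether the types of patients seen have changed and why. The drug-shop form lacks that direct question in the pages shown.

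**The case against.** The strongest case against has four parts.

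- **The unseen page.** The health worker questionnaire opens with a general section on changes at work. A similar opening for drug shops is plausible and might prompt some shops to mention a shift. This stands as a limit: the claim is confined to Section 3. A general question would still not repair the filter there.
- **Other sources.** Caregiver focus groups in both arms ask about sources of treatment and change at the nearest health centre. Community health worker groups ask about change in patient types. Section 4.5.1 also draws on ACT PRIME household surveys. These mean that the private-sector strand of objective 4 does not rest on this filter alone. They are, however, other people's accounts, and compensate only in part for the shops' own.
- **The setting.** Section 5.2 describes very high transmission, and section 1.1.1 says most patients are treated at home with drugs bought from informal shops. If malaria is a large share of trade, a real fall would show in the total and pass Qn 2. That is fair, and is why no frequency is claimed.
- **Draft status.** Piloting may find the fault. That makes it cheap to mend, not harmless if left.

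A reader might infer that the skip biases the study towards finding no private-sector effect, or hides a movement of malaria patients to health centres. The documents do not support either. The form records perceived change in up to 10 shops and gives no reliable effect estimate. No printed item records where customers went, so a movement to health centres would not be captured directly even without the skip.

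**Conclusion.** The point holds for Section 3 of the form as printed. Any answer but Yes to a question on total custom removes every structured item on malaria customers and drugs requested, together with the reason and the patient-load comments. Shifts within steady trade are therefore under-detected in that section, whichever way they run.

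The size is one tenth of the planned maximum sample for each shop affected. The number affected cannot be derived from the documents, and any stated fraction of shops lost would be a guess. The conclusion rests on interviewers following the written routing, and on page 1, which is not shown, holding no equivalent item. It is an avoidable loss on one strand of a secondary objective, worth correcting before fieldwork. It does not threaten the primary objective.

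**What to change.** Remove the skip after Qn 2 and ask every shop three separate items, each over the existing one-year window:

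1. Change in total customers: more, same, fewer.
2. Change in customers with malaria or fever: more, same, fewer.
3. Change in drugs requested: yes or no, and which.

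Keep don't know and refused codes on each. If any of the three changed, ask the reason, including whether customers now go elsewhere and where. Ask the patient-load comment of everyone.

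The recall window need not change: interviews fall about 9-12 months after roll-out, so a one-year look-back already reaches it, and shop workers may not know the roll-out date.

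The cost is a rewording of Qn 2 and Qn 3, a small change to the data entry screen, and about a minute more per interview. No extra shops, visits or analysis methods are needed, and the change can be made at the piloting stage in section 5.7.

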**3. "If so, what kind of changes have you noticed?"**

1 = More customers come to the drug shop  
2 = Fewer customers come to the drug shop [ ] [ ]  
3 = More patients with malaria come to the drug shop  
4 = Fewer patients with malaria come to the drug shop [ ] [ ]  
5 = Customers ask for different drugs (*specify*) [ ] [ ]  
\_\_\_\_\_  
77 = Other \_\_\_\_\_  
88 = Don't know  
99 = Refused to answer

*Record all answers given*

**SSQ: PRIVATE DRUG SHOPS (4)**

|                       |                    |                                               |
|-----------------------|--------------------|-----------------------------------------------|
| Drug shop code | Provider ID | Date                                   |
| [ ] [ ]               | [ ] [ ] [ ] [ ]    | [ ] [ ] / [ ] [ ] / [ ] [ ]
day month year |

**SECTION 3 cont: PATIENT LOAD**

4. "What do you think is the reason for this change?"

5. Please provide any additional comments about patient load at this drug shop.

**SECTION 4: PATIENT MANAGEMENT**

1. "What treatments do you most commonly recommend for children with fever?"

*Record all answers given*

- 1 = Artemether-lumefantrine (Coartem/Lumartem) [ ] [ ]  
 2 = Chloroquine + sulfadoxine-pyrimethamine (Homapak) [ ] [ ]  
 3 = Quinine [ ] [ ]  
 4 = Paracetamol (Panadol) [ ] [ ]  
 77 = Other \_\_\_\_\_ [ ] [ ]  
 88 = Don't know [ ] [ ]  
 99 = Refused to answer [ ] [ ]

2. "What treatments do you most commonly recommend for adults with fever?"

*Record all answers given*

- 1 = Artemether-lumefantrine (Coartem/Lumartem) [ ] [ ]  
 2 = Chloroquine + sulfadoxine-pyrimethamine (Homapak) [ ] [ ]  
 3 = Quinine [ ] [ ]  
 4 = Paracetamol (Panadol) [ ] [ ]  
 77 = Other \_\_\_\_\_ [ ] [ ]  
 88 = Don't know [ ] [ ]  
 99 = Refused to answer [ ] [ ]

3. "What treatments do you most commonly recommend for a patient with uncomplicated (simple) malaria?"

*Record all answers given*

- 1 = Artemether-lumefantrine (Coartem/Lumartem) [ ] [ ]  
 2 = Artesunate + amodiaquine [ ] [ ]  
 3 = Dihydroartemisinin-piperaquine (Duocotexcin) [ ] [ ]  
 4 = Any artemisinin-based combination therapy [ ] [ ]  
 5 = Quinine [ ] [ ]  
 6 = Chloroquine + sulfadoxine-pyrimethamine (Homapak) [ ] [ ]  
 77 = Other \_\_\_\_\_ [ ] [ ]  
 88 = Don't know [ ] [ ]  
 99 = Refused to answer [ ] [ ]

4. Please provide any additional comments about patient management at this drug shop.

SSQ: PRIVATE DRUG SHOPS (5)

|                |              |                          |
|----------------|--------------|--------------------------|
| Drug shop code | Provider ID  | Date                     |
| [ ][ ]         | [ ][ ][ ][ ] | [ ][ ] / [ ][ ] / [ ][ ] |
|                |              | day month year           |

SECTION 5: ADDITIONAL COMMENTS

Please use this space to provide any other comments

## APPENDIX X: FGD DATA COLLECTION TOOL

### Community health workers

#### PART 1: PARTICIPANT DETAILS

Record the demographic details for each participant using the primary caregiver or heads of household FGD participant log as appropriate.

#### PART 2: FGD INTRODUCTION

|                                                                                                                                         |                                                                          |
|-----------------------------------------------------------------------------------------------------------------------------------------|--------------------------------------------------------------------------|
| Subcountry ID [ ]                                                                                                                | Moderator initials [ ] [ ] [ ]                                    |
| FGD ID number [ ] [ ] [ ]                                                                                                        | Note-taker initials [ ] [ ] [ ]                                   |
| Location of village
1 = <2 km
2 = >2 km [ ] [ ]                                                                            | Gender of participants
1 = Male
2 = Female [ ] [ ]          |
| HFI or Standard care
1 = HFI
2 = Standard care [ ] [ ]                                                                     | Health center in parish
1 = Yes
2 = No [ ] [ ]              |
| Date:
[ ] [ ] / [ ] [ ] / [ ] [ ]

 
day
 
month
 
year
 
 | Time start [ ] [ ] : [ ] [ ]
Time end [ ] [ ] : [ ] [ ] |

